### Participant timeline

The scheduling of study phases is outlined in Fig. 1 with the overall study anticipated to run for a period of 24 months. This timeframe ensures that participants have sufficient time to receive an individualised service and to participate in a six-month post-intervention follow-up in order to ascertain to what extent any changes from either intervention are maintained, improved or have deteriorated over time. Enrolment into the study is on a phased basis and is dependent on the referral of job-seekers to activation and the GIS. Additionally, both the intervention and control group participation durations may vary per job-seeker, due to the individualised nature of the services, but will not exceed six months.

### Sample size

A power analysis was conducted using the primary outcome measure of overall psychological wellbeing (GHQ-12) in order to identify the minimum sample size required to detect an increase in wellbeing post intervention. As already indicated, the Pathways to Work activation model is a recently implemented approach and so no previous evaluations or comparable studies have been undertaken, although similar studies had been conducted in Sweden [51], France [52], Australia [6] the UK [41, 42] Finland [72] and the USA [53, 73]. Analysis of these studies indicate varying sample sizes (*n* = 16–1200); thus, to ensure the minimum sample size is achieved and the study is powerful enough to detect significant differences between the groups, a power analysis was performed to establish a realistic estimate based on the primary outcome measure. This analysis was conducted for an independent samples t-test, as this is expected to be the least powerful test in the overall main analysis. The analysis was two-tailed (alpha of 0.05), as we do not know in advance which group will perform better in GHQ-12 terms. G*Power t-test calculations for the difference between two independent means (two groups) show that for the current study, 128 unemployed participants (64 in each group) will be sufficient to detect a change of 0.50 (medium) at 80% power and at 5% significance at a given time point. An allowance of (approximately) 10% will be made for possible attrition, so the actual sample size target will be 70 per group. This should be more than sufficient for Mixed Model Repeated Measures (MMRM) across the three time points to have > 80% power and also allow for post-hoc t-tests both between groups and within groups to have ≥ 80% power.

### Recruitment

Participants in this study will be randomly selected from a pool of job-seekers, referred by the Intreo office to the NGO for activation (i.e. service as usual) on a weekly basis. Referred job-seekers consist of a mix of short- and long-term unemployed. The job-seeker is invited to attend the first step in the activation process which comprises a GIS where information on all supports and interventions offered by the public employment service and delivered through the DSP’s Intreo service, are outlined. The GIS normally occurs within two weeks of a social welfare claim being made; however, due to the large number of job-seekers in Ireland who are currently long-term unemployed (100,600 individuals accounting for 56.1% of total unemployment [CSO, Q1 2016]), an accumulation of job-seekers in the Intreo system has resulted in job-seekers who have not yet attended a GIS. In response to this, the Intreo office identifies a specified number of long-term unemployed job-seekers each week for referral to the NGO employment services. Currently, 60 job-seekers per week, with varying durations of unemployment, are drawn randomly from the live register for attendance at a GIS which is held in the NGO and delivered by a NGO staff member. The GIS is a standard presentation, designed by the DSP, and delivered nationwide to all job-seekers as part of their initial engagement with the employment services.

The list of job-seekers referred to the GIS is sent to the NGO data manager one week before the GIS. Clients are allocated to one of seven guidance practitioners and appointments made on the NGO appointments schedule. Clients attend the GIS and are informed of their appointment (i.e. given an appointment card with time and name of guidance practitioner for the following week). Client’s first appointments are with the researcher who at this point invites eligible clients to participate in the study and written informed consent is sought. This process will continue until adequate participant enrolment has been achieved for each group.

## Methods: assignment of interventions

### Allocation

#### Sequence generation and implementation

The participant’s initial appointment is with the researcher who explains the study and consent forms and administers the participant questionnaire. The researcher informs the data manager of those clients who agree to participate and who give informed consent. The data manager randomly assigns eligible participants to either the intervention or control group on a 1:1 basis using the SNOSE (sequentially numbered opaque sealed envelopes) method as described by Doig and Simpson [74]. Randomisation is conducted by the data manager only, ensuring that the randomisation is achieved without any influence from the researcher or the practitioners involved in the delivery of the service.

Seven practitioners deliver services to the intervention and control groups. Practitioners who deliver the intervention are not involved in delivering services to the control group (and vice versa) in order to ensure that practitioners deliver the service with fidelity and that there is no contamination between the intervention and control groups.

#### Allocation concealment mechanism and implementation

The data manager has been provided with 200 sealed envelopes containing a treatment allocation paper with either ‘Intervention A’ or ‘Intervention B’ (control group) printed on one side. Using the SNOSE (sequentially numbered opaque sealed envelopes) method as described by Doig and Simpson [74], the data manager allocates participants to either the Intervention or Control groups. Participants are also tagged on the NGO’s internal data management system as Intervention or Control group so that reports can be accessed at required junctures in the study. The data manager informs the researcher of any issues arising, such as a delay in referrals from Intreo, a break in the referral cycle or issues relating to randomisation.

### Blinding

After assignment to the respective interventions, the participants are blinded to allocation for the duration of the study. The researcher who performs the assessments at baseline is also blinded until the completion of baseline assessments. Due to the nature of the intervention, the staff delivering the interventions cannot be blinded and are instructed not to disclose information to either the researchers or the participants which may indicate which intervention the participant is receiving. Blinding of the researcher cannot be maintained post baseline as the researcher is also responsible for data collection in this study. For the participant, it remains unclear which intervention is being received as both interventions occur within the same site. For the researcher, knowledge of the staff responsible for each intervention and their caseloads indicates which intervention the client is receiving and therefore the blind is broken once the intervention starts.

The conditions under which the blind can be broken are limited to exceptional circumstances where the practitioner working with the client identifies the need to reveal the intervention. Such cases include situations where the allocated intervention is deemed harmful to the individual, particularly with regard to ancillary services, such as medical care, mental health care or social care. Practitioners will be required to discuss such cases in the first instance with the lead investigator (who is also an employment practitioner).

### Methods: data collection, management and analysis

#### Data collection methods

Participants are invited, as part of the trial, to complete a range of assessments at several time points (i.e. at baseline, at post intervention / ‘service as usual’ and six-month post-intervention follow-up) in order to measure the impact of the intervention or ‘service as usual’ on key dimensions including self-esteem, hopefulness, resilience and career self-efficacy (Fig. 1).

Each questionnaire (see Additional file 2) is coded with client ID, date of completion, researcher’s name, and questionnaire version (i.e. baseline, T1, T2). Client IDs are generated by the NGO and link to the client’s personal information contained on the NGO’s client database. This will be beneficial to the researcher at the six-month post-intervention phase in order to update data on the intervention or ‘service as usual’ and outcomes.

At baseline (T0), the study is explained to the potential participant and consent is sought (see Additional file 3). The baseline questionnaire is administered, coded and signed by the researcher. At post intervention (T1), the researcher meets with each participant, administers the questionnaire along with a participant update questionnaire which aims to capture information on re-employment, quality of employment, training progression and overall progress (see Additional file 4). This process is repeated at the six-month follow-up (T2).

A tracking file containing participant details—including client ID, completion of questionnaires, appointment dates, guidance practitioner name and outcome updates—will be maintained by the researcher for the duration of the study. Due to the nature of this client group, non-attendance is common and so a tracking system enables the researcher to identify ‘no-shows’, ‘drop outs’ and patterns of attendance. Outcome data for participants who do not continue or who deviate from the intervention or ‘service as usual’ will be documented in this file to study completion.

Practitioners to whom intervention clients are referred, are required to complete an in-depth profile for each participant relating to education, previous employment, skills, values, perceived employability and barriers to progression. These data will be held by the practitioner until the intervention is complete. All practitioners are required to administer the ‘P*erceived progress towards the labour market’* measure, Cantril’s Ladder, at baseline and post intervention, although some practitioners may choose to administer this on a more regular basis.

A small token in the form of a voucher is offered to each participant to help increase participation and to thank participants for their time in completing questionnaires at post intervention and at six-month follow-up.

#### Data management

Data management will be overseen by the researcher who will implement checks on a monthly basis to ensure the quality of the data collected and the accuracy of electronic data entry and coding. The researcher will gather all questionnaires completed at each time point and ensure the correct coding has been used and the appropriate date is on the front cover. This information will be entered into a database (IBM SPSS statistics version 22) on the researcher’s encrypted laptop and backed up every week on a separate removable storage device (also encrypted) which is stored safely in the researcher’s office. Data collected by practitioners will be gathered by the researcher post intervention and entered into the SPSS database for analysis. The tracking file will be updated by the researcher to ensure the visibility of each participant’s engagement with the service and their participation in the trial. All hard copies of questionnaires will be held securely in a locked cabinet for ten years after completion of the study, after which they will be destroyed. Participant identifiers will be stored separate from the data. The coding key and electronic raw data will be held securely for ten years and will then be destroyed by the researcher.

#### Statistical methods/analysis

The null hypothesis states that there will be no difference between the two groups in terms of primary outcomes (wellbeing) and secondary outcomes (self-esteem, career self-efficacy, resilience, hopefulness, perceived progress toward the labour market) at post intervention and at six-month follow-up. Descriptive statistics will be used to describe the pre-treatment characteristics of participants. Baseline analysis will be conducted to establish the internal consistency of the outcome measure scales, where a Cronbach’s alpha of above 0.7 will be required. Previous studies have reported Cronbach’s alphas of at least 0.7 across all measures*.*

The study will use a randomisation technique (the SNOSE [sequentially numbered opaque sealed envelopes] method as described by Doig and Simpson [74]) which ensures that participants from both groups come from the same population. Pre-treatment analysis will be conducted on primary and secondary outcome measures to show, for example, levels of wellbeing (primary outcome) as indicated by GHQ-12 scores in comparison with appropriate established norms *(e.g. national wellbeing data, HRB (2008))* so as to indicate how job-seekers present for activation services.

Mixed Model Repeated Measures (MMRM) will be used to investigate the effects of the intervention on primary and secondary outcome measures (i.e. wellbeing and employability). Continuous outcome data, including the primary outcome measure of wellbeing and five of the eight secondary outcomes which have been shown to contribute to mental health and increased employability (i.e. resilience, career-efficacy, hopefulness, self-esteem, perceived progress towards the labour market) will be analysed using MMRM. Where parametric test assumptions fail significantly, then non-parametric tests will be used.

MMRM will be used to investigate effects at two between (intervention and control) and three within (pre-intervention, post-intervention and six-month follow-up) levels. Initial MMRM analysis will control for age as a fixed co-variate, along with gender, and duration of unemployment or highest educational level, as applicable. Modelling for the primary outcome will be conducted using an unstructured repeated measures co-variance matrix and all other variables as fixed effects.

MMRM was chosen as the main statistical method for analysis as it can reduce several analytic problems that may arise from the EEPIC study design. First, it has the advantage of modelling change within individuals as well as across groups, thus enabling the isolation of factors contributing to the outcome, such as, age, gender, duration of unemployment or highest educational level (common to both intervention and control condition). Second, it allows for different numbers of measurements per participant, thereby tolerating a level of missing data, which are a particular problem with RCTs as follow-up data are often collected many months after treatment has ended and participants may be difficult to contact [75]. This enables us to use all of the data collected as opposed to deleting cases or imputing missing values. Third, it has the advantage of allowing for different time points for each individual, so data collected for one participant at month 4 can be tested alongside data collected for the next participant at month 6 [76]. Singer and Willet [77] identify this as the best approach for longitudinal data which has three or more time points.

The analysis will follow an intention-to-treat (ITT) principle where all randomised participants, including those who stop receiving the intervention, will be analysed ‘as randomised’. MMRM analysis is a maximum likelihood statistical modelling technique whereby mean estimates and the repeated measures covariance structure for the observed data are based on a statistical model and possible values are generated for the missing data [78]. Attrition will also be analysed to assess the differences between those who ‘dropped out’ and those who stayed, and indeed if there are predictors at baseline to indicate same. MMRM will be used in the main, although t-tests will be employed to detail any significant differences found from the MMRM.

In addition, descriptive statistical summaries (means, standard deviations, frequencies) will be presented for primary and secondary outcome measures at each time point (baseline, post intervention and six-month post intervention). Of most interest will be the identification of changes in primary and secondary outcome measures at group level between T0 (baseline) and T1, and T0 and T2, and between T1 and T2. Additional descriptive analysis (e.g. frequencies) of the re-employment (secondary) measure will be conducted to assess the differences between the two groups in terms of their re-employment outcomes.

Sub-group MMRM analysis will be conducted to investigate if the intervention effects differ for certain participant groups, based on variables such as gender, age, education level and unemployment duration. T-tests and Chi-squared tests will be employed to identify mean differences and associations with regard to primary and secondary outcome measures.

A full statistical analysis plan (SAP)—in the form of a Trials (free) update—will be provided once all data are gathered and before opening the database. Analysis will be conducted using SPSS software (IBM SPSS Statistics version 22).

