### Methods: monitoring

#### Data monitoring

A data monitoring committee is not feasible for this trial due to its short duration and size. The researcher will have sole access to the data and will monitor it monthly to ensure that the quality of data is maintained throughout the trial. Furthermore, within the context of this trial, an interim analysis is not practicable as sufficient data may not be available at the interim point for analysis. However, the researcher through monitoring of the data will inform the NGO, should any issues arise with the data collection, the recruitment of participants or the implementation of the intervention. This is of particular importance due to the ongoing changes in LMP implementation in Ireland and its very real bearing on the trial progress. Nevertheless, the flexibility of the NGO will ensure that should any changes to the trial be required, they will within reason be facilitated.

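### The plan lets unnamed non-parametric tests replace the primary MMRM without a criterion, and the SAP that would settle this is due only after an unblinded researcher has handled all the data

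*Protocol article*

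**What the plan says.** All references are to the protocol article.

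- **Primary method.** Statistical methods/analysis assigns MMRM to the primary outcome and to five of the eight secondary outcomes. The next sentence reads: "Where parametric test assumptions fail significantly, then non-parametric tests will be used".
- **Covariates.** The same section states: "Initial MMRM analysis will control for age as a fixed co-variate, along with gender, and duration of unemployment or highest educational level, as applicable".
- **What is fixed.** "Modelling for the primary outcome will be conducted using an unstructured repeated measures co-variance matrix and all other variables as fixed effects".
- **Why MMRM.** The section justifies it by adjustment for participant factors, by tolerance of unequal numbers of measurements, and by use of all collected data without deleting cases or imputing. The Discussion credits it with limiting attrition bias. Data collection methods warns that participants in this group often fail to attend.
- **SAP timing.** A full SAP "will be provided once all data are gathered and before opening the database".
- **Who holds the data.** Blinding states: "Blinding of the researcher cannot be maintained post baseline as the researcher is also responsible for data collection in this study", and adds that "the blind is broken once the intervention starts". Data management has the same researcher oversee an SPSS database on the researcher's own laptop, with monthly checks. Data monitoring states: "The researcher will have sole access to the data and will monitor it monthly".

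**The concern.** Two choices in the primary analysis stay open: whether MMRM is kept, and which third covariate enters it. The first matters more. If MMRM gives way to ordinary rank tests, the trial loses the features for which the protocol selected it, in a population where missed visits are expected.

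The order of events adds to this. The document that would close these choices follows the last data, and the person closest to the data knows the arms. A reader of a positive result could not tell whether the reported analysis was settled before the outcomes were seen.

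**Working it through.** **1. The plan's own figure.** Sample size gives 64 per group for a two-sided t-test (alpha 0.05, standardised difference 0.50, 80% power). With noncentrality 0.5 × √(64/2) = 2.83 on 126 degrees of freedom, power is 0.8015; at 63 per group it is 0.795. The figure reproduces and is not in dispute.

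**2. What the fallback drops.**

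| Feature for which MMRM was chosen | Standard two-sample rank test at one visit |
|---|---|
| All three time points modelled jointly | One visit at a time |
| Age, gender and a third covariate | None |
| Participants with a missing visit contribute through the likelihood | Only those observed at that visit |

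The last row bears on attrition bias. MMRM estimates remain valid if missingness depends on observed earlier values; a single-visit test uses no earlier values.

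**3. Type I error under no effect.** Simulation with 64 per arm and 5,000 runs per scenario. A baseline-adjusted linear model at one visit stands in for the MMRM contrast, and Mann-Whitney for the unnamed non-parametric test. Assumed, not in the documents: visit-correlation parameter 0.3, 0.5 or 0.7; normal or log-normal outcome; loading 0.2 for duration and for education; Shapiro-Wilk p < 0.05 as the trigger; no missing data. Ranges are over the six scenarios.

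| Conduct of the analysis | Rejection rate at nominal 5% |
|---|---|
| One pre-specified model | 4.4-5.4% |
| Switch applied mechanically by the fixed trigger | 4.6-5.6% |
| More favourable of the two third covariates | 5.4-6.2% |
| Most favourable of the two covariate sets and Mann-Whitney | 7.8-9.7% |

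The Monte Carlo standard error is √(0.05 × 0.95/5000) = 0.3 percentage points near 5%, and about 0.4 near 9%. The mechanical switch cannot be told from 5%; the last row clearly can. Allowing the same choice over both follow-up visits gave 14.9-16.6%, but that includes the separate multiplicity of two visits and is not charged to this point.

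**4. Power.** Simulation with 63 per arm, a shift of 0.5 SD, baseline correlation 0.5 (assumed) and 4,000 runs, with approximate results:

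| Outcome | Mann-Whitney | Baseline-adjusted model | Rank-based adjusted model |
|---|---|---|---|
| Normal | 78% | 89% | 87% |
| Skewed (chi-square, 3 df) | 94% | 88% | 97% |

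A repeat with a different seed agreed to within about 2 points. With normal data most of the gap comes from dropping baseline adjustment, not from ranking. With skewed data, the case most likely to trigger the switch, the rank test gains power under a shift.

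**5. Whether the SAP date protects.** Put together, the sections on Blinding, Data collection methods, Data management and Data monitoring show one researcher who administers the post-intervention and six-month questionnaires knowing the arms, oversees the database, checks it monthly and alone has access. For that person the database is in use long before the SAP is due.

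**The case against.** The strongest reply is that diagnostics, the named fallback and the final covariate list commonly belong in an SAP, which is not shown, and that the protocol commits to one. This largely disposes of the third covariate taken alone: age, gender and the unstructured covariance are already fixed, and free choice of the third covariate moves the error rate by about one point. It does not dispose of the switch, which the protocol itself states and which conflicts with its own reasons for MMRM. Nor does it dispose of the SAP date, which the protocol also sets.

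Four stronger readings are tempting, and the documents do not support them.

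- *A formal significance test of assumptions decides the switch.* The wording may only mean that assumptions fail substantially. Neither reading supplies a criterion.
- *Non-parametric tests cannot carry covariates or repeated measures.* Some rank-based and permutation methods can. The protocol names none, so the loss applies to the standard tests.
- *The fallback costs power.* Step 4 shows that this depends on the distribution.
- *The written rule inflates type I error, or the data will be mined.* A mechanical switch does not inflate it. The monthly checks are described as quality control, interim analysis is ruled out, and the documents do not say who types in the data or who writes the SAP. The risk lies in the opportunity; no misuse is planned.

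**Conclusion.** The point holds as a defect in a stated rule and in its timing. The protocol allows an undefined replacement of its primary analysis, and the standard form of that replacement would change the question and weaken the handling of missing visits. Requiring the SAP "will be provided once all data are gathered and before opening the database" gives limited protection, because an unblinded researcher already works with that database.

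The size is conditional. Type I error stays near 5% if the switch is mechanical, and reaches roughly 8-10% at one visit if the most favourable open option is selected. The upper figure rests on the assumed correlations, outcome distributions and covariate loadings, and on Mann-Whitney as the replacement. The change of question and of exposure to attrition bias rests on none of these except that a standard rank test is used. The point should be corrected; it does not invalidate the design or the sample size.

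**What to change.** 1. **Delete the switch.** Keep the MMRM primary whatever the diagnostics show. If residuals are clearly non-normal, use robust (sandwich) or bootstrap inference on the same model. Report rank-based analyses as named sensitivity analyses only.
2. **Name one covariate set now.** Age, gender, unemployment duration and education is one reasonable example. The cost is a few degrees of freedom if education is categorical (its number of levels minus one).
3. **Date and register the SAP now,** signed off by someone who has not seen outcome data by arm. The article reports 140 randomised but not how much follow-up is complete, so the SAP should state what data existed on its date. Masked arm labels would not be enough, because the researcher knows the practitioners' caseloads and keeps a tracking file with practitioner names.

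The cost is wording, an earlier SAP date and one independent sign-off. Sample size, visits and procedures do not change.

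### As written, the repeated-measures model gains no precision from the baseline score, and the claims that the t-test is the weakest test and that MMRM power exceeds 80% are not demonstrated

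*Protocol article*

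**What the plan says.** In the protocol article, the Statistical methods/analysis section makes MMRM the main method, to investigate "effects at two between (intervention and control) and three within (pre-intervention, post-intervention and six-month follow-up) levels". The pre-intervention score is thus one of three outcome levels. The covariates are age, gender, and either duration of unemployment or education. The baseline value of the outcome is not among them, and no constraint gives the two arms the same baseline mean. The covariance matrix is unstructured. The null hypothesis in the same section is about a difference between the groups at T1 and at T2.

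The section adds that "t-tests will be employed to detail any significant differences found from the MMRM". Among the descriptive summaries it says: "Of most interest will be the identification of changes in primary and secondary outcome measures at group level between T0 (baseline) and T1", and it lists the T0–T2 and T1–T2 changes as well.

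The Sample size section bases the number on an independent-samples t-test, "as this is expected to be the least powerful test in the overall main analysis". It then says that the resulting number gives the MMRM more than 80% power. It names no MMRM contrast, gives no correlation between visits and shows no MMRM calculation.

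**The concern.** The baseline questionnaire is completed before allocation, so randomisation makes the true baseline means of the two arms equal. A model that estimates a separate baseline mean for each arm does not use that fact. The T0 score then adds nothing to the comparison at a later visit. If the effect is tested as change from baseline, the noise in the T0 score is added to it.

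Three things are at stake.

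- **Precision.** The Trial status section reports that all 140 participants have been randomised, so further precision has to come from the analysis.
- **Follow-up tests.** Ordinary two-sample t-tests at a visit would leave out the covariates and anyone not seen at that visit. The section defends the MMRM because it keeps incomplete cases.
- **The power statement.** Whether the t-test is the weakest planned test, and whether the MMRM exceeds 80%, depends on which MMRM contrast is meant and on the correlation between baseline and follow-up.

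**Working it through.** **Inputs from the protocol article**

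- Two-sided alpha of 0.05 (Sample size).
- Effect, power and number: "128 unemployed participants (64 in each group) will be sufficient to detect a change of 0.50 (medium) at 80% power and at 5% significance" (Sample size).
- Attrition: "An allowance of (approximately) 10% will be made for possible attrition, so the actual sample size target will be 70 per group" (Sample size).
- Allocation to "either the intervention or control group on a 1:1 basis" (Sequence generation and implementation).

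**Assumptions, not in the document**

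- Correlation ρ between any two visits, shown from 0.2 to 0.8, with equal variances.
- Complete data and independent participants. Any gain from the demographic covariates and any clustering by practitioner are ignored.

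**Step 1: reproduce the plan's figure.** For n per group, power comes from a noncentral t with 2n − 2 degrees of freedom and noncentrality δ√(n/2). With δ = 0.5 and n = 64, the noncentrality is 0.5 × √32 = 2.83 and power is 80.1%. The stated 64 per group reproduces. With 70 per group power is 83.6%. With 70 × 0.9 = 63 per group it is 79.5%.

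**Step 2: variance of the treatment contrast,** relative to an unadjusted comparison at one visit. A generalised least squares calculation of the 2 × 3 model confirms these factors.

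- Contrast at a follow-up visit, baseline means free: 1.
- Change from baseline, baseline means free: 2(1 − ρ).
- Baseline means constrained equal, or baseline score as covariate: 1 − ρ².

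The adjusted factor is never the largest: 1 − (1 − ρ²) = ρ², and 2(1 − ρ) − (1 − ρ²) = (1 − ρ)². The change contrast is weaker than the t-test when 2(1 − ρ) > 1, that is, when ρ < 0.5.

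**Step 3: effective effect size,** 0.5/√factor.

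- ρ = 0.3: change 0.5/√1.4 = 0.423; adjusted 0.5/√0.91 = 0.524.
- ρ = 0.5: change 0.5/√1 = 0.500; adjusted 0.5/√0.75 = 0.577.
- ρ = 0.7: change 0.5/√0.6 = 0.645; adjusted 0.5/√0.51 = 0.700.

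**Step 4: power with 64 per group.** The last column is the 2-df group-by-time test (noncentral F) with effects of 0, 0.5 and 0.5 at T0, T1 and T2.

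| ρ (assumed) | Visit contrast | Change contrast | Baseline-adjusted | Group × time, 2 df |
|---|---|---|---|---|
| 0.2 | 80.1% | 60.2% | 81.7% | 62.1% |
| 0.3 | 80.1% | 66.0% | 83.7% | 68.4% |
| 0.4 | 80.1% | 72.7% | 86.5% | 75.5% |
| 0.5 | 80.1% | 80.1% | 90.0% | 83.2% |
| 0.6 | 80.1% | 88.1% | 93.9% | 90.8% |
| 0.7 | 80.1% | 95.2% | 97.6% | 97.0% |
| 0.8 | 80.1% | 99.3% | 99.7% | 99.7% |

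The change contrast reaches 80% at ρ of about 0.50 with 64 per group, or 0.45 with 70. The 2-df test with 64 per group reaches it at about 0.46. At ρ = 0.5 adjustment cuts the variance by 25% against either the visit or the change contrast (0.75 against 1).

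**The case against.** The strongest reply is that the stated null is a between-group difference at each follow-up visit. That contrast has 80.1% power with 64 per group and 83.6% with 70, whatever the correlation. This stands. A reader might infer that the MMRM cannot reach 80%, but the document does not support that. The change contrast and the 2-df test also exceed 80% once ρ is above about 0.50 and 0.46.

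The text does not say that the baseline means are free, and a baseline outcome level is not an error in itself, since the preferred remedy keeps it. That also stands. But without a stated constraint, an ordinary 2 × 3 fit estimates both baseline means, and the published covariate list leaves the score out.

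Three other strong readings go too far.

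- **That the main results will come from t-tests.** The section calls MMRM the main method and uses t-tests only to detail what it finds. It also does not say whether they would be on raw or change scores.
- **That within-group change is the primary inference.** The sentence on what is of most interest sits among descriptive summaries, and group-level change may mean change compared between groups.
- **That the test is a group main effect averaged over all three visits.** Its power would be only 63.0% at ρ = 0.5 with 64 per group, but no section names it as the test.

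Finally, a full SAP is promised before the database is opened and could settle the model. That lowers the urgency but does not remove the point, because the covariate set and the two power statements are already published.

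**Conclusion.** The point holds as a loss of precision and an undemonstrated power statement. Randomisation protects the comparison with or without adjustment, so there is no bias, and the sample size of 140 is not called into question.

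Against the visit contrast, the planned model forgoes about 4, 10 and 17 percentage points of power at ρ of 0.3, 0.5 and 0.7 (83.7, 90.0 and 97.6 less 80.1). Against the change contrast the shortfall is about 18, 10 and 2 points (83.7 − 66.0, 90.0 − 80.1, 97.6 − 95.2). These figures rest on the assumptions listed above, above all on ρ, which the document does not give.

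The statement that the t-test is the weakest test is not generally true: it fails for the change contrast when ρ is below 0.5. The statement that MMRM power exceeds 80% may be right, but it is asserted without the contrast or correlation on which it depends.

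**What to change.** 1. Name the between-group differences at T1 and at T2 as the contrasts of interest.
2. Keep the MMRM with three outcome levels, but constrain the arms to a common baseline mean: time effects plus a group effect at T1 and T2, with no group term at T0. This is preferred because it keeps every randomised participant. The alternative is T0 score × visit as a covariate, with T1 and T2 as outcomes. Its efficiency is similar, but it drops anyone with no follow-up.
3. Report the model-based adjusted differences with 95% CIs at T1 and T2 in place of the follow-up t-tests, and label within-group changes as descriptive.
4. In the Sample size section, state the contrast and assumed correlation behind the MMRM power claim, or remove it. Withdraw or qualify the statement that the t-test is the weakest test.

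The constraint is justified for scores taken before allocation. Practitioners collect the first Cantril's Ladder score during the service, so it needs separate thought.

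The cost is revised wording and one changed model statement. No new data are needed, and the change can go into the promised SAP before the database is opened.
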